### Study setting

The study aims to recruit patients in the community (primary care or public health responses) and in public hospitals. The mode of collection will either be a self-collect rectal swab (done by the patient themselves) and bulk faeces sample or clinician collect rectal swab and bulk faeces sample within a clinical environment. The generalisability of this trial is supported by its relatively broad inclusion and exclusion criteria, which are designed to reflect routine clinical practice. Because the trial aims to evaluate the use of rectal swabs as an alternative to bulk faeces sampling, eligibility is not restricted (e.g., based on symptom presentation), allowing for the inclusion of participants with diverse clinical profiles. This inclusive approach will mimic routine clinical practice, and facilitate recruitment across a broad range of demographic, clinical, and socioeconomic backgrounds, enhancing the external validity of the findings. Vulnerable groups, such as comorbid or immunocompromised individuals, are identified in the recruitment phase and this data is recorded to be used in the analyses. The lower age limit of 18 years has been set due to ethical and regulatory considerations in recruiting children and performing rectal swabs on a vulnerable group. While children are not included in this study, the trial findings relevant to rectal swab accuracy are expected to be applicable to all ages.

Inclusion criteria:

Persons aged 18 and older.Able to consent to and perform the additional rectal swab test.Close contact or person exposed, suspected, or confirmed case associated with an outbreak of an enteric organism. E.g., hepatitis A outbreak, foodborne outbreak.Chronic carrier of an enteric organism that requires testing.Person involved in a clinical encounter where they are or are likely suffering from a disease caused by an enteric organism. (E.g., person presenting to the GP or Emergency Department with diarrhoea or jaundice)

Exclusion criteria:

Persons unlikely (as judged by the clinician) to be harbouring an enteric organism.Persons where collection of a rectal swab is medically contra-indicated.

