### Consent

In all study settings, the potential participant will be asked by the treating clinician for consent to be contacted by the local study coordinator. After which the local study coordinator/study nurse will contact the person to obtain consent for inclusion into the study.

There will be two ways that a participant can consent to participating (verbal, written). Verbal consent will be obtained over the phone with a study coordinator or study nurse, as is commonly done in outbreak situations. The study nurse will read the patient information sheet to the participant over the phone, ensure the participant understands the process and document this in a database held on Queensland Health data servers. The testing pack will be sent to the participant and will include the patient information sheet about the study and all contact details for questions about the study. Furthermore, implicit consent will occur when the participant obtains both samples (the participant can decline to participate by not providing the rectal swab) and returns one or both samples to the pathology laboratory.

If the testing is done in person (a study clinician is present), verbal, written and implicit consent (the patient will obtain the sample themselves and return it to the study coordinator) will be obtained using the patient information sheet, and the signature document will be kept, with a copy offered to the participant.

Opting out of the study will be possible for participants at all stages of the study, up until the analysis of the research. For example, a participant may agree to participation over the phone, then, once they receive the full pack with the Patient Information Sheet, and they read over it in detail, they can withdraw from the study by calling us and withdrawing, or, not sending the rectal swab, and then withdrawing after we check in with them after the rectal swab was not returned.

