**Fig 2 pone.0329643.g002:**
[figure not shown]
Sample size analysis. Includes a range of parameters. The “Sensitivity priors” represents the approximate expected sensitivity of our method, and the “proportion positive” represents the proportion of samples that will contain an organism, which also means that should test positive.

Constrained resources (e.g., funding), demands a higher pre-test probability at the time of testing to estimate with confidence. For example, if we only have funding for 40 persons tested, we will elect to test persons with clear known linkages to a person with the illness (symptomatic family member of someone diagnosed with norovirus), or we would perform clearance testing in persons with known disease using these methods (the guidelines call for clearance testing for a variety of illnesses). With greater funding, testing can approximate normal clinical encounters and have less restrictive criteria for testing. If the funding is limited to 40 samples, we will endeavour to control the testing method, aiming for in-clinic self-testing.

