### Recruitment

The recruitment strategy will be multifaceted to obtain samples from a range of representative clinical settings, e.g., outbreaks, community, and in-hospital. The strategy will involve a central study coordinator supporting acquisition of samples, coordinating the multiple sources. For outbreaks, the study coordinator will be able to send sample collection packs to the patient, family, and/or symptomatic members of an outbreak via express post. In community settings, the study coordinator can obtain samples from GP practices that are seeing patients who were recently inpatients in hospital – identified from admission lists, or our Infectious Diseases Physician study collaborators. Inpatients, especially those which represent persons with a high pre-test probability, will be identified, recruited via their treating practitioner, and then consented to take part in the study. Consent will be performed verbally over the phone by a study coordinator (records kept locally), and/or with a physical form sent in a return envelope.

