#### Minimum data requirements.

At a minimum, data collected for each participant should include:

Identifiers (name, address, date of birth, contact details, comorbidities)Recruitment details (date of recruitment, date of consent, proof of consent, date that test packs were posted, symptomatology, duration of symptoms, presence of blood in faeces (if applicable))Sample collection details (where samples were collected (e.g., at home), who collected the sample (e.g., self-collect), date and time each sample was collected, date samples were submitted to pathology lab)Bulk faeces and rectal swab test results (date that lab testing was conducted for each sample, presence of visible faeces for the rectal swab only, positive/negative detection results for each sample)Follow-up information (date of follow-up attempts, which sample was collected first as reported by the participant, rough estimate of time difference between samples collected, adverse event details, preferred sample method)

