### Statistical methods

We will summarise safety and efficacy data using descriptive statistics, including means, medians, and frequencies. We will use statistical tests to compare groups (e.g., chi-square tests for categorical data, t-tests for continuous data). We will also adjust for multiple comparisons to control for type I error.

Logistic regression models will be used to assess accuracy in the presence of potential confounders. This includes sex (female/male), age (by age group), person collecting sample (self-collect/clinician collect), comorbidities, symptomatology (symptomatic/asymptomatic), duration of symptoms, and whether blood was present in the sample. Subgroup analysis will be conducted according to disease type (e.g., viral, or bacterial).

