#### Secondary outcomes.

We will calculate the number and percentage of participants experiencing at least one adverse event, and the total number of adverse events reported. We will tabulate the distribution of adverse events by severity (mild, moderate, severe) for both the rectal swab and bulk faeces groups. Summarise AEs by expectedness (expected, unexpected) and relatedness (definitely, probably, possibly, unrelated) for each group. We will report the incidence rates of adverse events per 100 participant-days for each group, allowing for comparison over different follow-up periods. We will use chi-square tests or Fisher’s exact tests to compare the incidence rates of adverse events between the rectal swab and bulk faeces groups. We will use ordinal logistic regression to analyse the severity of adverse events, treating severity as an ordinal outcome. We will include group (rectal swab vs. bulk faeces) as the main predictor and adjust for potential confounders (e.g., age, gender, mode of testing, and location of testing).

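### The accuracy model includes who collected the swab but not where, so a home effect specific to the swab would be read as an effect of self-collection

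*Protocol article*

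**What the plan says.** All references are to the Protocol article.

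- **Statistical methods:** "Logistic regression models will be used to assess accuracy in the presence of potential confounders". The factors named are sex, age group, "person collecting sample (self-collect/clinician collect), comorbidities, symptomatology (symptomatic/asymptomatic), duration of symptoms, and whether blood was present in the sample". That makes seven, and neither place of collection nor setting is among them.
- **Secondary outcomes (under Statistical methods):** the model for adverse event severity will "adjust for potential confounders (e.g., age, gender, mode of testing, and location of testing").
- **Minimum data requirements:** each participant's record includes "where samples were collected (e.g., at home), who collected the sample (e.g., self-collect"), with collection date and time and the date of submission to the laboratory. Data collection and management also lists setting and type of collection.
- **Study setting:** one of the two modes is "clinician collect rectal swab and bulk faeces sample within a clinical environment".
- **Recruitment:** for outbreaks the coordinator can "send sample collection packs to the patient, family, and/or symptomatic members of an outbreak via express post".
- **Consent:** with a study clinician present, "the patient will obtain the sample themselves and return it to the study coordinator", so self-collection also occurs on site.
- **Sample size calculation, text after Fig 2:** if funding allows only 40 samples, "we will endeavour to control the testing method, aiming for in-clinic self-testing".

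**The concern.** The trial has a single group, and nobody is randomised to self- or clinician collection. A swab from a posted kit is in practice self-collected away from the clinic, while clinician collection is described as happening in a clinical environment. Collector and place are therefore associated by design. A model with the first and without the second gives a collector coefficient that also contains any effect of place on the swab.

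This matters because the Introduction aims to validate self-collected and clinician-collected swabs alike, for clinical and public health use. A shortfall due to the patient's technique and one due to home collection or handling lead to different advice. The first questions self-collection itself. The second would still leave self-collection on site open. The listed model cannot tell them apart, although the data to do so are recorded.

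**Working it through.** **1. The two covariate lists side by side.**

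| Factor | Accuracy model | Adverse event severity model | Recorded? |
|---|---|---|---|
| Collector / mode | named | named | yes |
| Place / location | not named | named | yes |

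The protocol recognises location as a potential confounder next to mode, but only in the safety model.

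**2. Which effect counts.** Sensitivity is measured against the participant's own stool. If home conditions made both specimens negative, the pair would count as concordant negative and not as a swab miss. Only an effect on the swab that differs from the effect on the stool enters the collector term.

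**3. Illustration of size (assumptions, not protocol figures).** Assume no true collector effect, all clinician swabs taken in clinic, clinic sensitivity 0.95 (the planning value in Sample size calculation), home sensitivity S, and a share h of self-collected swabs taken at home. Then:

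- Sensitivity among self-collected swabs = h × S + (1 − h) × 0.95
- Apparent collector odds ratio = [that sensitivity / (1 − that sensitivity)] / (0.95 / 0.05)

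Example: S = 0.90 and h = 0.5 give 0.925. The odds are 0.925 / 0.075 = 12.33, and 12.33 / 19 = 0.65.

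| Home sensitivity S | h = 0.5 | h = 0.9 |
|---|---|---|
| 0.95 | 1.00 | 1.00 |
| 0.93 | 0.83 | 0.72 |
| 0.90 | 0.65 | 0.50 |
| 0.85 | 0.47 | 0.32 |

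The correct value in every cell is 1.00, and separating swabs by place restores it. The first row shows that there is no bias if place has no effect. If home swabs did better, the error would run the other way.

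**4. Can the two effects be separated?** Only if some self-collection takes place in clinic. With 30% to 50% of swabs clinician-collected, the variance inflation from the correlation between collector and place, 1 / (1 − φ²), is 1.3 to 1.5 when half of self-collection is at home and 3.7 to 5.5 when 90% is. At 100% they cannot be separated.

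**5. How much information there is.** The plan's 61 pairs reproduce as 1.96² × 0.95 × 0.05 / (0.10² × 0.30) = 60.8, rounded up. The half-width of 0.10 is inferred, since the text does not give it. Expected false negatives:

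- 61 pairs: 61 × 0.30 = 18.3 positives, × 0.05 = about 1
- 600 pairs at the cited 25% positive: 150 positives, × 0.05 = 7.5

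A sensitivity model with seven factors is already beyond what 7 or 8 events can support. This favours a table by group over further model terms.

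**6. Size of the within-clinic comparison.** With 150 positives, half of swabs self-collected and equal positivity across groups (both assumed), self-collected positives in clinic number 150 × 0.5 × 0.5 = 37.5 if half of self-collection is at home, and 150 × 0.5 × 0.1 = 7.5 if 90% is.

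**The case against.** The strongest reply is that no self versus clinician comparison is planned. Collector is listed as a potential confounder, the primary outcomes are 2x2 measures against stool, and each kind of swab is to be validated against stool and not against the other. This stands: a reader might infer a formal contrast, but the protocol announces none. The model nevertheless yields a collector coefficient, and it will invite that reading.

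The lists may also be open, since the accuracy list is introduced as an inclusion and the safety list as examples, and a fuller analysis plan could add location. That softens any charge of contradiction. It does not explain why location was named in one model and left out of the other.

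A reader might also infer that home swabs reach the laboratory later. The documents do not say so. Kits are posted out, return is to laboratories or collection points, and samples travel chilled. Nor is it stated how far place determines mode. The Study setting phrase about a clinical environment could qualify both modes, and on-site self-collection is foreseen. Patient type is partly covered by comorbidities, symptomatology and symptom duration.

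Finally, the stool normally comes from the same setting as the swab, and events will be few. Both points stand. They narrow the concern to a swab-specific effect and argue against adding many model terms.

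**Conclusion.** The point holds in limited form. The accuracy model omits a recorded factor that is tied to collection mode and that the protocol treats as a confounder elsewhere. Any swab-specific effect of home collection or handling would be attributed to self-collection.

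The size is unknown. The odds ratios of 0.83 to 0.32 for home sensitivities of 0.93 to 0.85 rest wholly on assumed values, and the bias is zero if place does not matter. It would be tempting to claim a definite false loss of sensitivity from self-collection, or a bias in the primary result. The documents support neither: they give no effect of place, and the overall 2x2 estimates do not pass through this model.

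**What to change.** In Statistical methods, replace the two-level collector factor with the recorded combination of collector and place: clinician-collected in clinic, self-collected in clinic, self-collected at home. Report sensitivity and specificity with 95% confidence intervals for each group. State that any self versus clinician comparison will use only swabs taken in a clinical setting.

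Describe collection-to-laboratory time by group. It need not be a required model term, given how few false negatives are expected.

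The change is one of analysis wording and uses data already collected. The within-clinic comparison will rest on fewer pairs with wider intervals, and it may be uninformative if few self-collected swabs are taken in clinic. In that case the report should say that the effects of collector and place could not be separated.

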The outcome of this project will transform clinical practice for doctors and patients. It will make testing far more convenient and allow for point-of-care testing to become a reality for enteric organisms. Currently, many people leave the emergency department without a faecal test because they could not produce a specimen while they were with the clinician. Rectal swabbing would make the diagnosis, and better care available for these patients. Public Health practitioners would be able to perform mass testing after small or large scale outbreaks, such as those caused by hepatitis A, norovirus or other organisms found in faeces [14,15]. Doctor’s in the emergency department would be able to obtain swabs on demand for testing that would expedite time spent in ED and, with the earlier diagnosis, length of stay in hospital. Most importantly, for patients, it means that they no longer must go home, wait until they need to have a bowel motion, and then return to the hospital or GP clinic with their sample, as it can be done on demand, on-site (in a private situation). Thus, rectal swabbing can transform clinical practice through earlier diagnosis, shorter length of stay’s and greatly improving the patient experience. This study aims to demonstrate that self-collected or clinician collected rectal swabs are a valid alternative method of testing when compared to bulk faeces testing for a wide range of enteric organisms such as bacterial, viral, and parasitic/protozoan. The intended outcome of this project is to replace bulk faeces testing with rectal swabbing in daily clinical and public health practice.

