#### Primary outcomes.

We will assess the sensitivity, specificity, positive and negative predictive value, and positive and negative agreement value, using 2x2 tables. The gold standard will be bulk faeces PCR testing. Sensitivity is the proportion of individuals with the disease who test positive with rectal swabs. We will assess the cycle threshold (CT) values using general linear models if the relationship is linear as expected and estimate the receiver operating curves and areas under the curve to assess for the potential to need differential CT value cutoffs. All results will be reported using 95% confidence intervals.

The R statistical suite will be used for all analyses and data visualisation. All estimates will be presented with 95% confidence intervals (CI). P-values <0.05 are deemed significant, and p-values <0.1 are considered trends.

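### The aim covers self-collected and clinician-collected swabs, but the analysis specifies no accuracy estimate for either mode, so a pooled sensitivity can mask a loss in one of them

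*Protocol article*

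**What the plan says.** The aim, in the Introduction of the protocol article, names both modes: "This study aims to demonstrate that self-collected or clinician collected rectal swabs are a valid alternative method of testing". Under Study setting each participant has one mode: "The mode of collection will either be a self-collect rectal swab (done by the patient themselves) and bulk faeces sample or clinician collect rectal swab". Modes are not randomised, and no quota or expected split is given.

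In Statistical methods, collector enters here: "Logistic regression models will be used to assess accuracy in the presence of potential confounders". The list that follows has seven items, one of which is "person collecting sample (self-collect/clinician collect". The subgroup analysis named in the same paragraph is by disease type: "Subgroup analysis will be conducted according to disease type (e.g., viral, or bacterial".

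Elsewhere:

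- The 2x2 tables under Primary outcomes are described without reference to mode.
- The stratified analyses and the 73-positive target under Sample size calculation are by pathogen.
- The margins under Interim analysis are for the swab as a whole against bulk faeces.
- Who collected the sample is part of the minimum data set.

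**The concern.** Collector defines the two things that the aim wants to validate, yet the plan handles it as a nuisance variable. A coefficient for collector describes how accuracy differs between modes after adjustment. It does not give the sensitivity of a self-collected swab against bulk faeces, which is what the aim asks for.

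Self-collection is where this matters most. Recruitment has kits posted to people in outbreaks, and the Introduction looks ahead to mass testing after outbreaks. The support cited for self-collection comes from human papilloma virus testing, another setting. If self-collected swabs lose sensitivity, a single overall figure could look satisfactory while the mode most needed outside hospital falls short.

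**Working it through.** **Inputs from the protocol article**

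- Expected sensitivity 95%; prevalence 20–30%, literature about 25%; fewer than 600 samples; 73 positives per pathogen subgroup (Sample size calculation).
- 3–6 swabs a week for two years (Timeline): 3 × 104 = 312 to 6 × 104 = 624 pairs.
- Significance level 0.05 (Primary outcomes), taken here as two-sided.
- Final margin 0.10 (Interim analysis). It is set for the swab overall and is used here only as a yardstick for a loss worth detecting.

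**Assumptions:** the split between modes; a true sensitivity of 95% for clinician-collected and 85% for self-collected swabs; 25% prevalence, so 600 pairs give 150 positives and 312 pairs give 78.

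**1. The plan's own figures.** Use n = 1.96² × Se × (1 − Se) / (d² × prevalence) with Se = 0.95.

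- d = 0.10, prevalence 0.30: 60.8, so 61 pairs.
- d = 0.10, prevalence 0.20: 91.2, so 92 pairs.
- d = 0.05, positives only: 72.99, so 73 positives.

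All three stated figures are reproduced. The values of d are inferred, because the text does not give them. None of the figures is by collection mode.

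**2. Masking.** Take 150 positives, 38 self-collected and 112 clinician-collected. Expected true positives are 38 × 0.85 + 112 × 0.95 = 32.3 + 106.4 = 138.7, or about 139. The pooled estimate is 139/150 = 92.7%, with exact 95% CI 87.3% to 96.3%. The interval lies wholly above 85%, the true value for self-collection in this example. The point estimate also agrees with the protocol's expectation of more than 90%.

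**3. What the collector term could detect.** Power for 95% against 85% among positives, two-sided 0.05, by enumerating all outcomes of two independent binomials. The unadjusted comparison stands in for the logistic term.

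| Positives (self / clinician) | Fisher | Chi-square | Likelihood ratio |
|---|---|---|---|
| 39 / 39 (312 pairs) | 17% | 34% | 35% |
| 112 / 38 (600 pairs) | 31% | 33% | 44% |
| 75 / 75 (600 pairs) | 45% | 55% | 56% |

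By normal approximation, 80% power with an equal split needs 141 positives per mode. That is 282 in all, or 282 / 0.25 = 1,128 pairs at 25% prevalence and 282 / 0.30 = 940 at 30%. Both exceed the stated ceiling of under 600.

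The protocol also promises: "We will also adjust for multiple comparisons to control for type I error". The method is not named. If it covered the collector term, power would be lower than shown.

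**4. Estimating each mode separately.** At the protocol's own subgroup standard, two modes need 2 × 73 = 146 positives. With an equal split that is 146 / 0.30 = 487 pairs or 146 / 0.25 = 584 pairs, which is within the ceiling.

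**The case against.** The best reply is that this is a condensed article. Its oversight section has statisticians writing analysis plans, and a table by collector could well appear there. The text does not say that disease type is the only subgroup, nor that the 2x2 tables must be pooled. The aim can also be read as concerning one swab strategy, whoever holds the swab. These points have weight, and they are why this is a matter of improvement and not of error. They do not remove it: the article does assign collector a role, and that role does not answer the aim as worded.

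Three stronger readings are tempting and are not supported.

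- A reader might infer that self-collection will be accepted if its coefficient is non-significant. No such rule is stated. The nearest text is a general convention, "P-values <0.05 are deemed significant, and p-values <0.1 are considered trends", and all estimates are to carry 95% confidence intervals.
- A reader might infer that a 10-point loss would usually be missed. That depends on the test, the final size, the prevalence and the split. With 75 positives per mode, chi-square or likelihood-ratio power is about 55%, and at 180 positives (600 pairs, 30% prevalence) split equally chi-square power is 63%. Fisher's test, which gives the lowest figures, is named in the protocol only for adverse events.
- A reader might treat mode as identical with setting. The sample size section contemplates self-testing in clinic, so the two overlap only in part.

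The masking example also depends on its split. With 112 of 150 positives self-collected, the expected pooled value is (112 × 0.85 + 38 × 0.95) / 150 = 131.3 / 150 = 87.5%, visibly below the planned 95%.

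**Conclusion.** The point holds in limited form. The aim covers both collection modes, while the stated analysis gives collector only an adjusting role and specifies no accuracy estimate or precision target for either mode. With a minority of swabs self-collected, a 10-point loss in that mode can sit behind a pooled estimate of 92.7% whose interval excludes the true 85%.

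A non-significant collector term could not be read as equivalence: power against that loss runs from 17% to 56% across the scenarios tabulated. These figures rest on an assumed split, 25% prevalence and an assumed contrast of 95% against 85%. The protocol fixes none of these by mode, and other choices move the power up or down. The change is worth making because it is cheap and answers the stated aim directly.

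**What to change.** In Statistical methods and Primary outcomes:

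- Name collection mode as a subgroup for the primary outcome.
- Report the 2x2 table, sensitivity and specificity with exact 95% confidence intervals separately for self-collected and clinician-collected swabs.
- Report the between-mode difference with its 95% confidence interval. Describe it as a non-randomised comparison, since setting is not among the covariates listed for the accuracy model.
- Base any conclusion about a mode on that mode's own estimate and interval, and state that a non-significant collector term is not evidence of equivalence.

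The data are already to be collected, so the analytic cost is small. The price is wider intervals per mode. Reaching 73 positives in each takes roughly 487–584 pairs with an equal split and more with an unequal one, so where a mode falls short its achieved precision should be stated.

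One practical matter needs settling. The de-identification section suppresses cells of 5 or fewer persons, and at 95% sensitivity 75 positives give 75 × 0.05 = 3.75 expected false negatives. The plan should say how tables by mode will be published under that rule.
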